## Abstract

**Highlights:**

## Introduction

Diverticular Disease (DD) is defined as clinically significant and symptomatic colonic diverticulosis and includes diverticular bleeding, diverticulitis, and Symptomatic Uncomplicated Diverticular Disease (SUDD) [1]. DD prevalence increases significantly with age, ranging from 10–20% in those younger than 40 years up to 50 to 70% in those older than 70–80 years [2,3]. While diverticulitis occurs in around 5% (1.7% complicated) of patients with diverticulosis [4], admission rate is steadily increasing overall and at a higher rate in younger patients [5]. Indeed, risk factors for DD such as obesity, diet low in fiber, lack of exercise, smoking, and aging of population are increasing. Along with the different clinical presentations and populations affected by DD, diagnosis and treatments have consistently changed. To standardize the treatments, several classifications have been proposed through the years, and several algorithms developed focusing on clinical features and patient’s quality of life more than anatomical and pathological landmarks [1,2,6,7,8]. Moreover, different surgical treatments have been proposed [8,9,10,11,12], while the surgical approach has been shifting to a minimally invasive approach even in the emergency setting [13,14]. Indeed, population, natural history, presentation, severity, and treatment for DD are heterogeneous, and optimal care for patients with DD needs high-quality evidence from large cohort studies [15]. Initial experiences of registry on DD recently appeared in the literature [16,17,18], suggesting the genesis of networks dedicated to DD as the best feasible way to strengthen clinical evidence. However, very few prospective cohort studies explore the outcomes between the different presentations and treatments for DD.

The Diverticular Disease Registry (DDR Trial), on behalf of the Advanced International Mini-Invasive Surgery (AIMS) academy clinical research network, will investigate both short-term 30-day postoperative outcomes and 12-months quality of life assessment in patients with DD. All different surgical and medical treatments will be explored to define the best management for each different presentation of DD. In addition, clinical parameters correlating with favorable outcomes in patients undergoing surgery or medical treatment for DD will be considered according to recurrence, health utilization, and mortality rates.

## Methods

### Study design

This protocol describes a multicenter, prospective, observational cohort study on diverticular disease. The DDR Trial is open to participation by all tertiary-care hospitals. The DDR Trial aims to investigate short-term postoperative and long-term quality of life outcomes in patients undergoing surgery or medical treatments for diverticular disease. The primary outcome is the quality of life assessment at 12-month in patients with diverticular disease according to the Gastrointestinal Quality of Life index (GIQLI) [19]. The secondary outcome is 30-day postoperative outcomes according to the Clavien-Dindo classification [20].

### Study population

After written informed consent, all consecutive patients encountered or admitted to a General Surgery or Gastroenterology Unit of a tertiary-care hospital with a diagnosis of DD will be enrolled in the DDR Trial. One investigator in each center, is responsible to preserve the informed consents, to update data collection, and to follow-up the patients through their medical record numbers. Patients will be enrolled in the DDR Trial starting from June 2021 and ending after 5 years of recruitment, according to the inclusion criteria.

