#### Inclusion criteria

All adult patients (≥18 years old) with colonic DD will be included. DD is defined as clinically significant and symptomatic colonic diverticulosis and includes diverticular bleeding, diverticulitis, and Symptomatic Uncomplicated Diverticular Disease (SUDD). Symptoms include but are not limited to fever, alternating bowel habits, pain, diverticular bleeding, and dysuria. The presence of colonic diverticulosis needs to be confirmed by imaging or during emergency surgery and/or by pathological diagnosis. After obtaining written informed consent, either patient presenting in an outpatient or emergency department will be enrolled. According to the European Society of Coloproctology guidelines [1], a colonoscopy confirming DD will be required during the follow-up or before surgical treatment, if feasible.

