#### Exclusion criteria

Patients with asymptomatic diverticulosis only (imaging or colonoscopy incidental finding of colonic diverticula without symptoms, evidence of acute inflammation or complication), with other concomitant bowel diseases (inflammatory bowel disease, colorectal cancer, and ischemic bowel), or without informed consent will be excluded.

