### Study variables

The DDR Trial’s variables will include patient baseline, presentation, diagnosis, treatment, and follow-up of patients enrolled, as reported in the CRF. Study variables will be documented for every patient’s presentations and treatments.

Patients enrollment and baseline will be recorded during the first surgical visit, together with a complete clinical examination. In particular, anthropometrics, habits, comorbidity, relevant medications, and baseline quality of life will be collected and categorized (CRF1- CRF2). Charlson comorbidity score adjusted for age will be calculated for every patient [21]. Patients older than 70 years old will be assessed for frailty risk using the modified Frailty Index described by Robinson et al. [22].

Patients and disease presentations are collected according to two different settings (from the emergency room or ambulatory/outpatient clinic). Symptoms, previous presentation, diagnosis, and treatments, need for admission, and treatment will be recorded (CRF3).

Instrumental diagnostic data from colonoscopy, abdominal computerized tomography (CT) and virtual CT colonoscopy be collected (CRF4).

Surgical pre- and intraoperative details will be recorded in the DDR Trial both for emergency procedures and for elective procedures, such as surgical setting, surgical procedure, resection, peritoneal lavage, laparoscopy, operative time, estimated blood loss, conversion, type of mesenteric artery ligation, stapler used and other technical aspects (CRF5). 30-day postoperative complications will be reported and graded according to the Clavien-Dindo classification [20]. Length of stay and post-discharge complications will be evaluated and recorded. Application of Enhanced Recovery After Surgery (ERAS) protocols will be considered valid if only at least 80% of the designed colorectal items will be satisfied [23].

Specimen length, the presence of microscopic and macroscopic abscesses, Crohn’s-like reaction, lymphocyte infiltration, and unknown cancer will be obtained by the pathology report for patients who underwent surgical resection (CRF6).

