Follow-up will be done yearly assessing patient status, time to recurrence, symptoms, medication, consideration of surgical intervention, and quality of life (CRF7). Quality of life will be evaluated according to the Gastrointestinal Quality of Life index (GIQLI) [19]. The GIQLI is a 36-item patient reported outcomes instrument designed to assess GI-specific health-related quality of life in clinical practice and clinical trials of patients with GI disorders. It has five domains (GI symptoms, emotion, physical function, social function and medical treatment) and subscores range from 0–4 while the total score range from 0–144. Higher scores mean better GI health-related quality of life [19]. In addition, Female Sexual Function Index (FSFI) [24], International Consultation on Incontinence Questionnaire (ICIQ) [25], International Index of Erectile Function (IIEF) [26,27], and International Prostate Symptom Score (IPSS) [28], will be used, as appropriate.

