### Data analysis plan

Data analysis will primarily explore the quality of life in patients with DD after different treatments. Secondly, we aim to evaluate surgical management and short-term 30-day postoperative outcomes. We will explore baseline covariants that may identify clinical parameters correlating with favorable outcomes or be predictive of failure in patients undergoing different treatments for DD. Furthermore, we will evaluate recurrence, successive presentations (health utilization), and mortality rates. No personal or hospital-specific comparisons will be performed. The results of the DDR Trial will be reported according to the STROBE statement [31].

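### Patients enter at any point of a relapsing disease, but the named treatment comparisons are unadjusted and have no stated time zero, so earlier course may confound them

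*Protocol article*

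**What the plan says.** All references are to the protocol article.

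- **Entry.** Study population takes "all consecutive patients encountered or admitted to a General Surgery or Gastroenterology Unit of a tertiary-care hospital with a diagnosis of DD". Inclusion criteria add "All adult patients (≥18 years old) with colonic DD will be included". Exclusion criteria remove "Patients with asymptomatic diverticulosis only", other concomitant bowel disease and absence of consent. Earlier episodes, earlier medical treatment and earlier resection are no bar.
- **History.** Study variables expects patients with a past: "Symptoms, previous presentation, diagnosis, and treatments, need for admission, and treatment will be recorded (CRF3"). It also provides for baseline quality of life on CRF1 and CRF2, and for documenting each presentation and treatment.
- **Timing.** Study variables states "Patients enrollment and baseline will be recorded during the first surgical visit". Study design sets the primary outcome as GIQLI at 12 months without saying from when. For recurrence the text is "Follow-up will be done yearly assessing patient status, time to recurrence, symptoms, medication, consideration of surgical intervention, and quality of life", again with no origin.
- **Analysis.** Data analysis plan states "Data analysis will primarily explore the quality of life in patients with DD after different treatments", and describes baseline covariates as a search for predictors of success or failure. Statistical analysis names t-test or ANOVA, or their rank equivalents, for continuous data, logistic regression on unnamed covariates, and Kaplan-Meier as the example of survival analysis.

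**The concern.** The Introduction aims to identify the best management for each form of presentation, and the Discussion expects the follow-up data to support management recommendations. Those are comparative aims. The Discussion also says that treatment is decided individually, according to presentation, setting, surgical expertise and patient preference. The number of earlier episodes and an earlier resection can plausibly influence both the treatment chosen and the later quality of life or recurrence. If so, an unadjusted comparison attributes to the current treatment what belongs to the patient's history.

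The missing time zero adds to this. Without a stated index presentation, a first recurrence and a later one can share a single Kaplan-Meier curve, and the 12 months of the primary outcome can start at different points of the course in different patients.

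**Working it through.** **Is there a figure to reproduce?** No. The article gives no sample size, GIQLI standard deviation, recurrence rate or share of patients with earlier episodes. The numbers below illustrate a mechanism and do not estimate this registry's bias.

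**1. What the text commits to.** The data needed to separate patients by history are collected (CRF3 and baseline quality of life). The tests named for a continuous score use none of them. The only covariate model named is logistic, which does not suit a GIQLI total analysed on its 0 to 144 scale. No stratification of the Kaplan-Meier curves is mentioned.

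**2. GIQLI, with no true treatment effect.**

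Bias = (difference between treatment groups in the share with earlier history) × (shift in 12-month GIQLI due to that history), taking the shift as the same in both groups.

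Assumed ranges: share difference 0.10 to 0.40; shift 5 to 15 points; SD 20 to 25; 100 to 500 patients per group. With SE = SD × √(2/n), the chance that the two-sided 5% test declares a difference is Φ(bias/SE − 1.96) + Φ(−bias/SE − 1.96).

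| Share difference × shift | Bias (points) | n per group | SD 20 | SD 25 |
|---|---|---|---|---|
| 0.10 × 5 | 0.5 | 100 | 5.4% | 5.2% |
| 0.20 × 15 (or 0.30 × 10) | 3.0 | 300 | 45.1% | 31.2% |
| 0.40 × 15 | 6.0 | 500 | 99.7% | 96.7% |

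For the middle row at SD 20: SE = 20 × √(2/300) = 1.633; 3.0/1.633 = 1.837; Φ(1.837 − 1.96) = 0.451, and the other tail is negligible. With a share difference of 0 the bias is 0.

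**3. Recurrence, with no true treatment effect.**

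Group risk = p × r1 + (1 − p) × r0, where p is the share with earlier episodes, r1 the risk with them and r0 the risk without. All values are assumed.

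- r0 = 10%, r1 = 20%, p = 0.3 against 0.5: 13% against 15%, ratio 1.15.
- r0 = 10%, r1 = 30%, p = 0.3 against 0.7: 16% against 24%, ratio 1.5.

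**4. Overall recurrence rate, no treatment comparison.** Suppose 80% of new patients relapse at 5% a year and 20% at 30%.

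- New patients: 0.8 × 5% + 0.2 × 30% = 10%.
- Patients entering in proportion to their relapse rate: high-risk share 6/10 = 60%, so the rate is 0.4 × 5% + 0.6 × 30% = 20%.
- Half-and-half mix: 15%, which is 1.5 times 10%.

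With milder rates (8% and 20%) the figures are 10.4%, 12.6% and 11.5%, or 1.1 times. This shows how an encounter-sampled mixture can differ from a first-episode cohort in its overall rate. It says nothing about a difference between treatments, or about GIQLI.

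**The case against.** The strongest objection is that all-comer entry is intended. The registry sets out to describe symptomatic disease as it presents to tertiary care and never claims a first-episode population. Recurrence is inflated only by comparison with a population the article does not target. That stands, and the entry rule is not an error.

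A second objection is that strata and adjustment factors commonly sit in a statistical analysis plan, which may exist but is not shown, and that the article does announce covariate modelling in general terms. That stands in part. Silence on covariates would be no finding by itself. But the article does state methods, those for a continuous score are unadjusted, and the primary outcome and time to recurrence are given no origin.

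A reader might also infer more than the text supports:

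- *That quality of life is lowered and recurrence raised mainly in the conservatively managed group.* If patients with repeated episodes are operated on more often, the imbalance falls on the surgical group. The article says only that treatment is individual.
- *That a previously resected patient now managed conservatively counts as medically treated, or that recurrence is timed from enrolment.* The article defines neither the treatment groups nor the origin.
- *That this is selection which adjustment cannot repair.* For the treatment comparison, the relevant covariate is earlier history, and it is recorded.

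Finally, making first presentations the only main comparison set would push aside patients with earlier presentations. Some of them may belong to the elective-surgery grey zone that the Discussion wants clarified. That objection stands and shapes the fix.

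**Conclusion.** The point holds as a risk of confounding, not as a demonstrated distortion. As written, the comparison of 12-month GIQLI after different treatments, and any comparison of recurrence, may be confounded by earlier episodes and earlier resection. This requires that history differs between treatment groups and affects the outcome. Individual treatment choice makes the first plausible, but the document does not establish either.

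Direction and size are unknown. The ranges above (0.5 to 6.0 GIQLI points; recurrence risk ratio 1.15 to 1.5) rest wholly on assumed inputs and fall to nil when histories are balanced. The 1.1- to 1.5-fold figure concerns one overall recurrence rate and should not be read as bias between treatments. The change is worth making as a cheap improvement on the stated analysis and gives no reason to alter eligibility.

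**What to change.** Keep all-comer enrolment. In the analysis plan:

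1. Take the enrolling presentation as the index, and as time zero for the 12-month GIQLI and for time to recurrence.
2. From CRF3, class each patient as first presentation, previously presenting (by number of earlier episodes) or previously resected.
3. Compare 12-month GIQLI with a linear model containing treatment, that class and baseline GIQLI. This assumes that the baseline quality-of-life measure is the GIQLI and that its score is kept, not only a category.
4. Stratify or adjust the recurrence analysis by the same class, for example with stratified Kaplan-Meier curves and a Cox model.
5. Report previously resected patients as their own group, and the first-presentation subset as a sensitivity analysis.

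The cost is a few sentences and a little more analysis work, with no new data. Strata will be smaller and estimates within them less precise. Adjustment covers only the history that CRF3 captures; unrecorded reasons for choosing a treatment remain.

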#### Inclusion criteria

All adult patients (≥18 years old) with colonic DD will be included. DD is defined as clinically significant and symptomatic colonic diverticulosis and includes diverticular bleeding, diverticulitis, and Symptomatic Uncomplicated Diverticular Disease (SUDD). Symptoms include but are not limited to fever, alternating bowel habits, pain, diverticular bleeding, and dysuria. The presence of colonic diverticulosis needs to be confirmed by imaging or during emergency surgery and/or by pathological diagnosis. After obtaining written informed consent, either patient presenting in an outpatient or emergency department will be enrolled. According to the European Society of Coloproctology guidelines [1], a colonoscopy confirming DD will be required during the follow-up or before surgical treatment, if feasible.

#### Exclusion criteria

Patients with asymptomatic diverticulosis only (imaging or colonoscopy incidental finding of colonic diverticula without symptoms, evidence of acute inflammation or complication), with other concomitant bowel diseases (inflammatory bowel disease, colorectal cancer, and ischemic bowel), or without informed consent will be excluded.

#### Patients enrollment

Following patient enrollment, study variables will be collected as patients progress through routine care pathways. Patients’ presentation and treatment may range from mild DD to peritonitis and from non-antibiotic treatment to surgery, respectively. Every patient’s presentations and treatment regimens will be recorded with the appropriate case report forms (CRF).

### Study variables

The DDR Trial’s variables will include patient baseline, presentation, diagnosis, treatment, and follow-up of patients enrolled, as reported in the CRF. Study variables will be documented for every patient’s presentations and treatments.

Patients enrollment and baseline will be recorded during the first surgical visit, together with a complete clinical examination. In particular, anthropometrics, habits, comorbidity, relevant medications, and baseline quality of life will be collected and categorized (CRF1- CRF2). Charlson comorbidity score adjusted for age will be calculated for every patient [21]. Patients older than 70 years old will be assessed for frailty risk using the modified Frailty Index described by Robinson et al. [22].

Patients and disease presentations are collected according to two different settings (from the emergency room or ambulatory/outpatient clinic). Symptoms, previous presentation, diagnosis, and treatments, need for admission, and treatment will be recorded (CRF3).

Instrumental diagnostic data from colonoscopy, abdominal computerized tomography (CT) and virtual CT colonoscopy be collected (CRF4).

Surgical pre- and intraoperative details will be recorded in the DDR Trial both for emergency procedures and for elective procedures, such as surgical setting, surgical procedure, resection, peritoneal lavage, laparoscopy, operative time, estimated blood loss, conversion, type of mesenteric artery ligation, stapler used and other technical aspects (CRF5). 30-day postoperative complications will be reported and graded according to the Clavien-Dindo classification [20]. Length of stay and post-discharge complications will be evaluated and recorded. Application of Enhanced Recovery After Surgery (ERAS) protocols will be considered valid if only at least 80% of the designed colorectal items will be satisfied [23].

Specimen length, the presence of microscopic and macroscopic abscesses, Crohn’s-like reaction, lymphocyte infiltration, and unknown cancer will be obtained by the pathology report for patients who underwent surgical resection (CRF6).

Follow-up will be done yearly assessing patient status, time to recurrence, symptoms, medication, consideration of surgical intervention, and quality of life (CRF7). Quality of life will be evaluated according to the Gastrointestinal Quality of Life index (GIQLI) [19]. The GIQLI is a 36-item patient reported outcomes instrument designed to assess GI-specific health-related quality of life in clinical practice and clinical trials of patients with GI disorders. It has five domains (GI symptoms, emotion, physical function, social function and medical treatment) and subscores range from 0–4 while the total score range from 0–144. Higher scores mean better GI health-related quality of life [19]. In addition, Female Sexual Function Index (FSFI) [24], International Consultation on Incontinence Questionnaire (ICIQ) [25], International Index of Erectile Function (IIEF) [26,27], and International Prostate Symptom Score (IPSS) [28], will be used, as appropriate.

### Data management

The Diverticular Disease Registry is managed using Research Electronic Data Capture (REDCap), a secure web-based platform designed to support databases for research studies [29,30]. Data will be prospectively uploaded in the Diverticula Disease Registry by the local principal investigator for each hospital via personal REDCap accounts. Quarterly meetings will be set between the study coordinators and the participating centers. The local principal investigator might be assisted by one or more collaborators according to the volume of the uploaded data. One investigator in each center will be responsible for the follow-up data. A data manager (AP) will regularly control the quality of the data provided, missing or implausible data will be identified and addressed.

### Data analysis plan

Data analysis will primarily explore the quality of life in patients with DD after different treatments. Secondly, we aim to evaluate surgical management and short-term 30-day postoperative outcomes. We will explore baseline covariants that may identify clinical parameters correlating with favorable outcomes or be predictive of failure in patients undergoing different treatments for DD. Furthermore, we will evaluate recurrence, successive presentations (health utilization), and mortality rates. No personal or hospital-specific comparisons will be performed. The results of the DDR Trial will be reported according to the STROBE statement [31].

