#### Statistical analysis

Categorical data will be summarized by frequencies and percentages, and compared using the chi-squared test. Continuous data will be summarized by mean and standard deviation (normally distributed data) or median and interquartile range (non-normally distributed data), and will be compared using the t-test or ANOVA (normally distributed data) and Mann-Whitney U test or Kruskal-Wallis test (non-normally distributed data), as appropriate. Logistic regression models will be developed to examine the relationship between outcomes and covariates. Survival analysis (e.g., Kaplan-Meier) will be used to study the time-to-event. A two-sided p-value <0.05 will be considered statistically significant.

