## Discussion

Although DD is a common condition, we continue to struggle in defining optimal care as DD is still poorly understood. The primary aim of the DDR Trial is to prospectively collect data on patients with DD, focusing on the clinical presentation, diagnosis, treatments, and clinical follow-up.

Standardizing the data collection of patients with diverticulitis is often tricky for clinical and logistic reasons. Indeed, patients with DD have different healthcare accesses: emergency department, endoscopic unit, surgical, and gastroenterological outpatient departments. Moreover, these patients might be admitted to a surgical or gastroenterological ward. As a consequence, the multiplicity of clinical scenarios results in a lack of accuracy in generating a register that collects clinical data. Herein, we want to pave the way to a collaborative, comprehensive, and user-friendly tool that aims to provide prospective clinical data.

Reaching scientific evidence about medical and surgical treatment of DD is extremely demanding, and it requires considerable resources. Therefore, high-quality evidence is limited, and frequently recommendations have low levels of evidence. Moreover, the decision-making process for DD treatment is determined on a case-by-case basis according to the different clinical presentations, settings, surgeon expertise, and patient preferences [15]. In addition, the decision for elective surgery for SUDD or smouldering diverticular disease (SDD) truly belongs to a clinical grey zone that needs to be clarified. Overall, because these clinical nuances are frequently present in daily practice and so hardly intelligible, it becomes clear the need for a structured outcome-related prospective registry. Indeed, follow-up data for patients with SUDD o SDD, either after surgical or conservative treatments, will provide high-quality evidence for management recommendations and practical decision making.

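### The stated aim is best management for each presentation, but the analyses named do not compare treatments within a presentation, and the covariate associations they yield are prognostic

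*Protocol article*

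**What the plan says.** The Introduction sets the aim: "All different surgical and medical treatments will be explored to define the best management for each different presentation of DD". The next sentence adds a further aim: "In addition, clinical parameters correlating with favorable outcomes in patients undergoing surgery or medical treatment for DD will be considered". The Conclusions return to identifying optimal care, and the Discussion expects follow-up of patients with SUDD or smouldering disease, after surgery or conservative treatment, to support management recommendations.

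Under Data analysis plan, the primary analysis is: "Data analysis will primarily explore the quality of life in patients with DD after different treatments". The covariate search is listed separately: the investigators will "explore baseline covariants that may identify clinical parameters correlating with favorable outcomes or be predictive of failure in patients undergoing different treatments".

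Under Statistical analysis, categorical data are compared by the chi-squared test. Continuous data "will be compared using the t-test or ANOVA (normally distributed data) and Mann-Whitney U test or Kruskal-Wallis test". For covariates: "Logistic regression models will be developed to examine the relationship between outcomes and covariates". Kaplan-Meier is the example given for time-to-event data, and significance is two-sided at 0.05.

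On how patients come to a treatment, the Discussion says that "the decision-making process for DD treatment is determined on a case-by-case basis according to the different clinical presentations, settings, surgeon expertise, and patient preferences".

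**The concern.** Choosing the best management for a presentation requires the difference in outcome between treatments among patients with that presentation. To say that a baseline parameter should guide the choice also requires evidence that this difference changes with the parameter. The named analyses supply neither. The between-treatment tests are not split by presentation and carry no adjustment, although the article itself says that presentation drives the choice of treatment. The logistic models are described only as relating outcomes to covariates, which estimates prognosis.

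Two misreadings of the results are at stake. A prognostic factor could be taken as a reason to prefer one treatment. A crude difference between treatment groups could be taken as a treatment effect when it reflects who was given which treatment.

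**Working it through.** The article states no sample size, event rate or effect size, so there is no figure of its own to reproduce. The check sets aim against analysis and then illustrates the gap. All risks and sizes below are assumptions, not values from the document.

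**Aim against analysis**

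- Needed for the aim: outcome on treatment A against treatment B, within each presentation, allowing for how treatment was chosen.
- Named: quality of life after different treatments (no split by presentation stated), unadjusted group tests, logistic models of outcomes on covariates, survival analysis.
- Not named: a comparison within presentation, a treatment-by-presentation or treatment-by-covariate contrast, or adjustment for treatment choice.

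**A covariate association within one treatment does not identify the better treatment**

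Assume 20% failure on medical treatment when the covariate is absent (x=0; odds 0.20/0.80 = 0.25) and a covariate odds ratio (OR) of 3 on medical treatment. When it is present (x=1) the odds are 0.75 and the risk is 0.75/1.75 = 42.9%.

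| | Medical x=0 | Medical x=1 | Surgery x=0 | Surgery x=1 | Covariate OR, medical | Covariate OR, surgery |
|---|---|---|---|---|---|---|
| A: surgery OR 0.6 at both levels | 20.0% | 42.9% | 0.15/1.15 = 13.0% | 0.45/1.45 = 31.0% | 3.0 | 0.45/0.15 = 3.0 |
| B: surgery OR 1.5 at x=0, 0.6 at x=1 | 20.0% | 42.9% | 0.375/1.375 = 27.3% | 0.45/1.45 = 31.0% | 3.0 | 0.45/0.375 = 1.2 |

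- In A, surgery minus medical is -7.0 points at x=0 and -11.8 points at x=1. The covariate is a strong marker of failure on both treatments, yet the better treatment is the same at both levels.
- In B, the differences are +7.3 and -11.8 points, so the better treatment reverses.
- The covariate OR on medical treatment is 3.0 in both. Only the contrast between treatments separates A from B: the ratio of ORs is 3.0/3.0 = 1.0 in A and 1.2/3.0 = 0.4 in B.

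**An unadjusted comparison of treatments can mislead when severity drives the choice**

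Assume no treatment effect, half the patients severe, failure 20% if mild and 42.9% if severe, and surgery given to 20% of mild and 60% of severe patients.

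- Failure on surgery: (0.5×0.2×0.200 + 0.5×0.6×0.429)/0.40 = 37.1%.
- Failure on medical treatment: (0.5×0.8×0.200 + 0.5×0.4×0.429)/0.60 = 27.6%.
- Crude OR: (0.371/0.629)/(0.276/0.724) = 1.55, entirely from confounding by indication.

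**Only if models were fitted and read separately by treatment**

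Simulation of 20,000 cohorts per setting, with the same covariate OR in both groups, overall failure 20% and the covariate present in 30%. Wald tests were used, with 0.5 added to each cell.

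| Operated / medical | OR | Significant in exactly one group | Interaction test significant |
|---|---|---|---|
| 200 / 800 | 1.5 | 55% | 4.6% |
| 200 / 800 | 2.0 | 52% | 4.7% |
| 150 / 350 | 1.5 | 37-38% | 4.7% |
| 150 / 350 | 2.0 | 55% | 4.8% |

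In the first row the parameter is significant in 21% of operated and 59% of medical groups, so exactly one occurs in about 0.21×0.41 + 0.59×0.79 = 55%. If 20% is taken as the risk without the covariate, the four figures for exactly one group are about 57%, 48%, 39% and 54-55%.

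**The case against.** The strongest reply is that this reads too much into a condensed article. Four parts of it deserve an answer.

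- **Separate models per treatment are not stated.** This is correct. The text refers to patients undergoing different treatments, and a pooled model with treatment and interaction terms would fit the sentence on logistic regression. A reader might infer that each treatment gets its own model and that a parameter significant in one group only will be called specific to that treatment. The article describes no such step, so the simulation shows a risk under that reading and is not a property of the plan.
- **The covariate search is not the route to best management.** This is also correct. The Introduction presents it as an additional aim, and the primary analysis is listed separately. It would be wrong to conclude from the covariate sentence alone that the main aim goes unanswered. The other named route does not close the gap, however, because it has no stated split by presentation and uses unadjusted tests.
- **Exact model terms belong in a full protocol or SAP.** Agreed: a missing interaction term would not by itself be a finding. What remains concerns what the article does state, namely an aim per presentation set beside analyses that yield prognosis and crude contrasts.
- **An interaction term would not settle the question either.** This stands and shapes the remedy. Treatment is not randomised, so a treatment-by-parameter term adjusted only for presentation and that parameter remains open to confounding by indication. Some presentations may also have too few patients on an alternative treatment to support a comparison.

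It can also be said that predicting failure is ordinary language for a prognostic model. That is fair, and labelling the results as prognostic removes the ambiguity.

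**Conclusion.** The concern holds as a mismatch between aim and named analysis. The article promises to define the best management for each presentation, while the analyses it names do not contrast treatments within a presentation or allow for how treatment was chosen. Associations between covariates and outcome among treated patients are prognostic and do not show who does better on which treatment.

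The documents fix no size for the problem. Under the assumed risks, an identical OR of 3.0 on medical treatment is compatible with opposite implications for the choice at x=0 (-7.0 against +7.3 points), and confounding by indication alone produces a crude OR of 1.55. Other assumed risks would change these values but not the logic.

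The documents do not support the stronger claims that the covariate search makes the aim unanswerable, or that treatment-specific predictors will be artefacts of unequal group sizes. The change is advisable and cheap, and it does not call the data collection into question.

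**What to change.** In the Data analysis plan and Statistical analysis sections:

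1. For outcomes defined identically across treatments (12-month GIQLI, recurrence, death), state a comparison of treatments within each presentation. Take it from a model with treatment, presentation, their interaction, and adjustment for baseline covariates already collected that drive treatment choice, such as baseline quality of life, comorbidity, frailty where assessed, and emergency or outpatient setting.
2. Report each treatment difference with its 95% confidence interval, and limit the comparison to presentations in which more than one treatment is actually used.
3. Report covariate-outcome associations as prognostic. Describe a parameter as possibly modifying the treatment effect only on adjusted treatment-by-parameter evidence, and then as hypothesis-generating, because treatment choice is not random. Such evidence should not by itself support a treatment recommendation.
4. If this comparison will not be made, soften the Introduction's best-management aim and the matching statements in the Discussion and Conclusions.

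The cost is wording and modest extra analysis on data already planned. Interactions have less power than main effects, so fewer parameters will be claimed as guiding treatment. Surgeon expertise and patient preference, which the Discussion names as drivers of choice, are not among the variables the article lists. Some confounding may therefore remain after adjustment and should be acknowledged.
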